### Recruitment and screening

2.4

Screening procedures will be conducted after obtaining informed consent (Table 2). These include the collection of demographic data, comprehensive medical history, a full physical examination encompassing height, weight, and vital signs, and ECOG performance status. Laboratory assessments will cover complete blood count, urinalysis, blood chemistry, coagulation, tumor markers, cardiac enzymes, thyroid function, and serology for hepatitis B virus (HBV), hepatitis C virus (HCV), and human immunodeficiency virus (HIV). Patients with positive HBsAg must undergo an HBV DNA test, and those with positive HCV antibodies requires an HCV RNA test. Women of childbearing potential must undergo a serum β-HCG test. Cardiac safety will also be assessed via electrocardiograms, and echocardiography. Tumor imaging will be performed using contrast-enhanced computed tomography (CT) or magnetic resonance imaging (MRI) of the abdomen, pelvis, and chest. Quality of life (QoL) scores will be recorded at baseline according to EORTC QLQ-C30 or QLQ-BIL21.

**TABLE 2 T2:** Schedule of patient visits and assessments.

Study period	Screening		Treatment		Follow-up	
Visit window *a*	Within 2 weeks prior to C1D1	Within 1 week prior to C1D1	Within 1 week prior to C2-xD1	Every 8 weeks ( ± 1 week)	4 weeks ( ± 1 week) after EOT	Every 12 weeks ( ± 1 week) after EOT
Clinical assessments						
Demographics	✓	​	​	​	​	​
Medical history	✓	​	​	​	​	​
Physical examination *b*	​	✓	✓	​	✓	​
ECOG performance status	​	✓	✓	​	✓	​
Quality of life	​	✓	​	✓	✓	​
Adverse events	​	​	✓	​	✓	​
Concomitant medications	✓	​	✓	​	✓	​
Electrocardiograms	✓	​	✓	​	✓	​
Echocardiogram	✓	​	​	​	✓	​
Laboratory assessments						
Complete blood count	​	✓	✓	​	✓	​
Urinalysis	​	✓	✓	​	✓	​
Blood chemistry test	​	✓	✓	​	✓	​
Coagulation test	​	✓	✓	​	✓	​
HBV, HCV, and HIV test *c*	✓	​	​	​	✓	​
Tumor markers test	​	✓	✓	​	✓	​
Cardiac enzymes test	​	✓	✓	​	✓	​
Thyroid function test	​	✓	✓	​	✓	​
Pregnancy test *d*	​	✓	​	​	✓	​
Tumor assessment						
CT/MRI imaging *e*	✓	​	​	✓	✓	​
Biomarker exploration						
Tumor sample	​	✓	​	​	​	​
Blood sample	​	✓	✓	​	​	​
Follow-up						
Survival status	​	​	​	​	​	✓
Subsequent therapy	​	​	​	​	​	✓

Abbreviations: C1D1, cycle 1 day 1; C2-x, cycle two and subsequent cycles; CT, computed tomography; ECOG, eastern cooperative oncology group; EOT, end of treatment; HBV, hepatitis B virus; HCG, human chorionic gonadotropin; HCV, hepatitis C virus; HIV, human immunodeficiency virus; MRI, magnetic resonance imaging.

Footnotes.

a Cycle Definition: Each treatment cycle is 3 weeks. Assessments listed under the Treatment column are to be performed prior to drug administration on day 1 of cycle two and subsequent cycles. Cycle 1 day 1 assessments are covered under Screening.

b Physical Examination: Includes vital signs (blood pressure, heart rate, respiratory rate, temperature), height, and weight.

c HBV, HCV, and HIV, Test: Includes HBsAg, HBsAb, HBeAg, HBeAb, HBcAb, HCV, antibody, and HIV, antibody screening. Patients with positive HBsAg must undergo further quantitative HBV DNA, testing. Patients with positive HCV, antibody must undergo further quantitative HCV RNA, testing.

d Pregnancy Test: Only applicable to women of childbearing potential. A serum β-HCG, test must be performed within 7 days prior to the first dose and at the safety follow-up visit.

e Tumor Imaging: Contrast-enhanced CT, or MRI, of the chest, abdomen, and pelvis. Scans performed during Screening serve as the baseline. Subsequent scans are performed every 8 weeks (±7 days), until disease progression or withdrawal of consent. The same imaging modality should be used throughout the study.

### Data collection and assessments

2.5

Tumor response will be evaluated every 8 weeks according to RECIST version 1.1. Given the mechanism of immunotherapy, pseudoprogression is a possibility. If disease progression is suspected radiologically but the patient is clinically stable, treatment may continue, and a confirmatory scan will be performed at least 4 weeks later, utilizing irRECIST criteria.

Safety will be assessed continuously throughout the study. Adverse events will be graded according to NCI-CTCAE version 5.0. Assessments will include physical examinations, ECOG performance status, and comprehensive laboratory panels (complete blood count, urinalysis, blood biochemistry, coagulation, tumor markers, cardiac enzymes, and thyroid function) performed within 1 week prior to the start of each new cycle. QoL scores will be collected every 8 weeks.

As the single-agent pharmacokinetic profile of JDB153 has been established in a prior phase I study (unpublished data), sparse sampling in cycle one combined with trough concentration monitoring in subsequent cycles is sufficient to assess potential drug-drug interactions while minimizing patient burden. Blood samples will be collected pre-dose, and at 2, 4, and 8 h post-dose in cycle 1 only.

Biomarker exploration is a key component of this trial. Patients will consent to the use of archival tumor tissue previously obtained and blood samples collected within 1 week prior to treatment. Analyses will include PD-L1 expression, mismatch repair (MMR) status, single-cell spatial proteomics and transcriptomics, and next-generation sequencing (NGS). PD-L1 is evaluated as a predictive marker for immunotherapy response and is mechanistically linked to JDB153 activity via MNK-eIF4E-mediated translational regulation. Peripheral blood markers will include T-cell subsets, heat shock protein 90α, and cytokines (IL-6, IL-8, IL-17, CRP) to capture dynamic immune changes and identify potential predictive biomarkers for treatment response.

### Interventions and dose modifications

2.6

Differentiation between targeted therapy toxicity and immune-related adverse events will be guided by timing of onset, histologic findings when available, and response to corticosteroids. Management of adverse reactions follows a stepwise approach based on severity. Appropriate supportive care will be administered, such as antidiarrheals for diarrhea, antiemetics for nausea, and hepatoprotective agents for liver dysfunction.

Dose adjustments for JDB153 are based on toxicity grades. If a ≥ grade 3 TRAE occurs, the JDB153 dose may be reduced to 500 mg BID. If a ≥ grade 3 TRAE recurs, a further reduction to 400 mg BID is permitted. More than two dose reductions and dose re-escalation after a reduction are not permitted. A new treatment cycle may begin only when neutrophils ≥1.5 × 10^9/L, platelets ≥75 × 10^9/L, and non-hematologic toxicities have recovered to ≤ grade 1. If treatment is interrupted for more than 2 weeks due to hematological toxicity, JDB153 should be permanently discontinued.

Dose reductions for serplulimab are not permitted. If toxicity results in a treatment delay of more than 12 weeks for any grade ≥2 adverse event that does not recover to grade ≤1, serplulimab will be permanently discontinued (Table 3).

**TABLE 3 T3:** Treatment adjustment for serplulimab-related adverse events.

Immune-related adverse event	Severity	Treatment adjustment
Severe cutaneous adverse reaction	Suspected SJS, TEN, or DRESS	Suspend use
	Confirmed SJS, TEN, or DRESS	Permanently discontinue
Colitis	Grade 2	Suspend use *a*
	Grade 3 or 4	Permanently discontinue
Hepatitis	ALT or AST: >3 to ≤5× ULN (>3 to ≤5× baseline if baseline is abnormal); orTotal bilirubin: >1.5 to ≤3× ULN (>1.5 to ≤3× baseline if baseline is abnormal)	Suspend use *a*
	ALT or AST: >5× ULN (>5× baseline if baseline is abnormal); orTotal bilirubin: >3× ULN (>3× baseline if baseline is abnormal)	Permanently discontinue
Pneumonitis	Grade 2	Suspend use *a*
	Grade 3 or 4	Permanently discontinue
Endocrine toxicity *b*	Grade 3 or 4	Suspend use until clinically stable, or permanently discontinue for severe cases
Nephritis	Grade 2 or 3 creatinine increased	Suspend use *a*
	Grade 4 creatinine increased	Permanently discontinue
Nervous system toxicity	Grade 2	Suspend use *a*
	Grade 3 or 4	Permanently discontinue
Myocarditis	Grade 2, 3, or 4	Permanently discontinue
Ocular toxicity	≥ Grade 2 toxicity not resolved to grade 1 within 2 weeks with local treatment, or requiring systemic treatment	Permanently discontinue
Infusion-related reaction	Grade 1 or 2	Interrupt infusion or reduce infusion rate
	Grade 3 or 4	Permanently discontinue
Other irAEs	Grade 2 or 3 (based on type and severity)	Suspend use *a*
	Grade 3 or 4 encephalitis; orGrade 3 or 4 Guillain−Barre syndrome; orGrade 4 or recurrent grade 3	Permanently discontinue

Abbreviations: ALT, alanine aminotransferase; AST, aspartate aminotransferase; DRESS, drug reaction with eosinophilia and systemic symptoms; irAE, immune-related adverse event; SJS, Stevens-Johnson syndrome; TEN, toxic epidermal necrolysis; ULN, upper limit of normal.

Footnotes.

a Treatment may resume when the adverse event resolves to grade 0–1 and the daily corticosteroid dose has been tapered to ≤10 mg prednisone (or equivalent). If the adverse event does not resolve to grade 0–1, or if the corticosteroid dose cannot be reduced to ≤10 mg/day prednisone equivalent within 12 weeks, serplulimab must be permanently discontinued.

b Depending on clinical severity, treatment may be withheld for grade 2 endocrine toxicities until symptoms improve with hormone replacement therapy. Treatment may resume once acute symptoms have resolved.

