### Study design

2.2

The study employs a Simon’s two-stage design, which permits early termination for futility and minimizes patient exposure to an ineffective regimen. The initial phase (phase Ib) will enroll 10 participants to evaluate the safety and preliminary efficacy of the combination. Patients will receive JDB153 at a dose of 600 mg orally twice daily (BID) and serplulimab at a dose of 200 mg via intravenous infusion every 3 weeks. If no patient achieves an objective response, the study will be terminated. The study will also be terminated in the event of unresolved SAEs or death. If one or more patient achieves, the trial will proceed to phase II. This phase will enroll additional patients to reach a total sample size of 32. If more than one patient in the phase Ib experiences a DLT, the dose of JDB153 for the phase II cohort will be reduced to 500 mg orally BID. Otherwise, the dose will remain at 600 mg orally BID. If DLT occur in one or more patients at the 500 mg BID dose level, the study will be terminated. If four or more responses are observed among the 29 evaluable patients, the null hypothesis will be rejected, indicating that the regimen merits further investigation.

Treatment will continue until documented disease progression (PD), intolerable AEs, withdrawal of consent by the patient, or a maximum duration of 24 months.

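### The JDB153 reduction ladder offers no lower dose at a first grade 3 or higher related event to a patient who starts phase II at 500 mg BID

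*Protocol article*

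**What the plan says.** Section 2.2 (Study design) treats phase Ib patients at 600 mg BID. If more than one of them has a DLT, "the dose of JDB153 for the phase II cohort will be reduced to 500 mg orally BID"; otherwise phase II stays at 600 mg BID. So two phase II starting doses are possible.

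Section 2.6 (Interventions and dose modifications) holds the only reduction rule for JDB153 in individual patients. At the first event: "If a ≥ grade 3 TRAE occurs, the JDB153 dose may be reduced to 500 mg BID". At the next: "If a ≥ grade 3 TRAE recurs, a further reduction to 400 mg BID is permitted". A cap follows: "More than two dose reductions and dose re-escalation after a reduction are not permitted". The doses are fixed amounts, not steps down from whatever the patient is taking, and no separate wording covers a 500 mg start.

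Section 2.2 also has a trial-level rule for the lower dose: "If DLT occur in one or more patients at the 500 mg BID dose level, the study will be terminated".

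**The concern.** The ladder fits a 600 mg start and no other. A patient who starts at 500 mg BID and has a first grade 3 or higher treatment-related event is offered the dose already being taken. The next level, 400 mg BID, is tied to a recurrence.

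The 500 mg branch opens only after 600 mg BID has caused more than one DLT, which is when a usable first reduction matters most. Safety is a primary endpoint (section 2.1), and treatment can last up to 24 months. At stake is a small matter of patient safety and consistent dosing, not the validity of the efficacy test.

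**Working it through.** **1. Dose steps by starting dose** (sections 2.2 and 2.6; step = current dose − ladder dose)

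| Start | First event | Recurrence |
|---|---|---|
| 600 mg BID | 600 − 500 = 100 mg | 500 − 400 = 100 mg |
| 500 mg BID | 500 − 500 = 0 mg | 500 − 400 = 100 mg |

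The 600 mg row uses exactly the two reductions allowed. The 500 mg row has one real reduction, and only at the second event.

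**2. Does another stated rule supply a lower dose?**

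- The recovery criteria, including "non-hematologic toxicities have recovered to ≤ grade 1", decide when a cycle may start, not at what dose.
- "If treatment is interrupted for more than 2 weeks due to hematological toxicity, JDB153 should be permanently discontinued" ends the drug for one type of delay and lowers nothing.
- "Treatment will continue until documented disease progression (PD), intolerable AEs, withdrawal of consent by the patient" ends treatment.
- The stop at 500 mg BID is triggered by a DLT, the ladder by any grade 3 or higher related event. Section 2.1 lists DLTs and treatment-related events separately, and the article does not define a DLT.
- Table 3 covers serplulimab only.

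None of these closes the gap.

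**3. How many patients?** The article states no DLT or event rates, so the rates below are assumptions. From the document come n1 = 10, at least one response needed to continue, ORR of 5% or 20% (section 2.7), and 32 − 10 = 22 phase II patients.

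*Chance that the branch opens.* It needs at least 2 DLTs and at least 1 response in 10 patients, taken as independent.

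- P(2 or more DLTs) = 1 − (1−p)^10 − 10p(1−p)^9 = 0.264, 0.624 and 0.851 at p = 10%, 20% and 30%.
- P(1 or more responses) = 1 − 0.95^10 = 0.401, or 1 − 0.80^10 = 0.893.
- Products: 0.106 to 0.236, 0.250 to 0.557, and 0.341 to 0.759.

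*Expected 500 mg starters.* Patients are taken one after another, up to the first DLT or 22 patients, with DLT rate q at 500 mg: (1 − (1−q)^22)/q = 17.9, 13.5, 9.0 and 5.0 at q = 2%, 5%, 10% and 20%.

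*If the branch opens,* with a 20% chance per patient of a non-DLT event of grade 3 or higher: 3.6, 2.7, 1.8 and 1.0 patients.

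*Overall,* multiplying by the branch probability, with a lower DLT rate at 500 mg than at 600 mg:

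| DLT rate at 600 / 500 mg | Event rate 10% | Event rate 20% | Event rate 40% |
|---|---|---|---|
| 10% / 5% | 0.14–0.32 | 0.29–0.64 | 0.57–1.27 |
| 20% / 10% | 0.23–0.50 | 0.45–1.00 | 0.90–2.01 |
| 30% / 20% | 0.17–0.38 | 0.34–0.75 | 0.68–1.51 |

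Each range runs from ORR 5% to ORR 20%. Stops for unresolved SAEs or death would lower these figures.

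**The case against.** The strongest reply is that this is a condensed article. Its ladder was written for the planned 600 mg dose, and a modification table for each starting dose may sit in the full protocol. That would answer a silence, but here both rules are stated in full, with doses and triggers, and as stated they do not fit together.

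A second reply is that a 500 mg cohort is already one level down the sequence 600, 500, 400, so 400 mg BID is naturally next. This is a sensible guess at the intent. But the text attaches 400 mg to a recurrence and does not say that a cohort-level reduction counts as a patient's first step. Sites could read it either way.

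Third, if every grade 3 or higher related event at 500 mg were a DLT, the trial would stop and the ladder would never be used there. This stands as a limit: without a DLT definition, the share of events outside that term cannot be read from the article.

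Fourth, the counts may be too high.

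- The patient whose DLT stops the trial is included. This is no overcount if the 20% is each patient's overall chance of a non-DLT event. If it applies only to patients without a DLT, each figure is multiplied by (1 − q): the 20%/10% pair becomes 0.41–0.90 and the 30%/20% pair 0.27–0.60.
- Immune-related events handled by holding serplulimab may not call for a JDB153 reduction, so the true number may be lower still.

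Finally, reduction is optional for everyone, dosing waits for recovery, and 400 mg BID remains available on recurrence. All of that is true and limits the harm.

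**Conclusion.** The point holds and is minor. As written, the ladder gives a 500 mg starter a first step of 0 mg, and no other rule in the article fills the gap. The loss is one optional 100 mg step, for grade 3 or higher related events that are not DLTs, in one branch of the design.

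The dose arithmetic is exact and needs no assumption. The patient counts rest on assumed rates, independence of DLT and response, and patients being assessed one after another. At the 20% event rate they come to about one patient or fewer in the trial, and to about two at most with a 40% rate. The Simon design, its error rates, the sample size and the ORR decision rule are untouched.

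**What to change.** Reword the ladder in section 2.6 relative to the current dose and keep it optional: *after a grade 3 or higher TRAE, JDB153 may go down one level from the current dose (levels 600, 500 and 400 mg BID)*. Add that 400 mg BID is the floor, which allows at most two reductions from a 600 mg start and one from a 500 mg start.

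A 500 mg starter could then go to 400 mg BID at the first event, and the steps for 600 mg starters stay as they are. The cost is a small rewording in one section, with no extra patients, visits or procedures and no change to the Simon design.

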### Statistical analysis

2.7

The sample size is calculated based on a Simon’s two-stage optimum design. The null hypothesis (P0) assumes a historical ORR of 5% for second-line treatment, while the alternative hypothesis (P1) anticipates an ORR of 20%. With a one-sided alpha of 0.05 and a beta of 0.2, the first-stage enrollment is 10 patients (n1 = 10), with a futility boundary of 0 responders (r1 = 0). The total planned enrollment is 29 patients (n = 29), with a rejection boundary of three responders (r = 3). Accounting for a 10% dropout rate, the total enrollment target is 32 patients.

Analyses will follow the intention-to-treat principle. The full analysis set and per-protocol set will be used for efficacy, while the safety analysis set will cover all patients who received at least one dose of the study drug.

Continuous variables will be presented as mean ± standard deviation or median with range, and categorical variables as frequencies and percentages. ORR and DCR will be reported with 95% Clopper-Pearson confidence intervals. Time-to-event endpoints (OS, PFS, DoR, TTP) will be estimated using the Kaplan-Meier method. Univariate and multivariable Cox proportional hazards models will be used to explore the impact of baseline characteristics and biomarkers on survival outcomes. Multivariable Cox regression models will include prior treatment characteristics as covariates to adjust for potential heterogeneity in baseline therapies. All statistical tests will be two-sided with a significance level of 0.05, performed using SPSS version 22.0 or higher.

## Discussion

3

Current clinical practice offers no established standard of care for patients with pancreatic cancer who progress after two lines of systemic therapy (National Comprehensive Cancer Network, 2025). These patients typically present with poor performance status and high symptom burden, limiting their ability to tolerate further intensive cytotoxic regimens. There is an urgent need for effective strategies that extend survival without compromising quality of life. This study aims to evaluate the safety and efficacy of a chemotherapy-free strategy using JDB153 combined with serplulimab.

ICIs have revolutionized the treatment of most solid tumors, such as melanoma and lung cancer (Topalian et al., 2015; Wu, 2022). However, they have historically failed to demonstrate meaningful efficacy in pancreatic cancer. This failure is primarily due to the “cold” nature of the pancreatic tumor microenvironment, characterized by a dense stroma and few immune cells (Ullman et al., 2022; Fan et al., 2020). Current guidelines recommend immunotherapy mainly for patients with microsatellite instability-high (MSI-H) or mismatch repair deficiency (dMMR) (National Comprehensive Cancer Network, 2025), but this group represents only about 1.0%–2.5% of patients (Grant et al., 2021; Ahmad-Nielsen et al., 2020; Luchini et al., 2021). Even within this biomarker-selected population, the efficacy in pancreatic cancer is modest. The KEYNOTE-158 trial reported an ORR of 18.2% and a median OS of 4.0 months (Marabelle et al., 2020). Previous trials attempting to combine immunotherapy with standard chemotherapy have also produced disappointing results (Renouf et al., 2022; Fu et al., 2023; Cheng et al., 2024; Wainberg et al., 2020; Kamath et al., 2020). Therefore, new strategies are needed. Remodeling the tumor microenvironment through combination therapies to relieve immunosuppression may be key to increasing sensitivity to immunotherapy (Zhang et al., 2022). For example, a phase II study combined the HDAC inhibitor entinostat with nivolumab in advanced pancreatic cancer. Among 27 evaluable patients, three achieved PR, with a median DoR of 10.2 months. Although the primary endpoint was not met, it showed that modifying the tumor microenvironment can help overcome resistance (Baretti et al., 2024). Similarly, a phase I study of the FAK inhibitor defactinib combined with pembrolizumab and gemcitabine showed a DCR of 80% and a median OS of 8.3 months in refractory pancreatic cancer (Wang-Gillam et al., 2022).

MNK is the only kinase that can directly regulate eIF4E activity (Buxade et al., 2008). However, MNK inhibitors alone have a limited ability to suppress eIF4E phosphorylation and tumor growth, and require combination with other agents (Li et al., 2023). Clinical data supports that targeting the MNK pathway can reprogram the immune landscape and make tumors more responsive to ICIs. A phase II study of the MNK inhibitor eFT508 combined with PD-1 blockade showed the regimen was well-tolerated and achieved partial responses in heavily pretreated patients. The most common grade 3 or 4 TRAEs were increased liver enzymes and rash, and about 18% of patients discontinued treatment due to AEs (El-Khoueiry et al., 2020). Another phase II study showed that eFT508 combined with avelumab had acceptable safety and preliminary activity in colorectal cancer. Common AEs included diarrhea, constipation, fatigue, myalgia or arthralgia, hypercalcemia and rash (Hubbard et al., 2019). Additionally, preliminary data from the KICKSTART trial in non-small cell lung cancer suggested MNK inhibition might enhance pembrolizumab activity. Although the OS data was immature and the PFS results did not meet statistical significance, there was a signal of efficacy. However, grade 3 or 4 AEs were more common in the combination arm compared to the placebo arm (67% vs. 37%) (Flaherty, 2024).

Combining anti-angiogenic agents with ICIs can promote the maturation of antigen-presenting cells and the activation of T cells. It also reduces the number of suppressive cells in the tumor (Kudo, 2020). Recent studies in pancreatic cancer have validated this approach. The NASCA trial evaluated surufatinib (a VEGFR inhibitor) combined with an anti-PD-1 antibody and chemotherapy. It reported a significantly improved ORR of 51.1% compared to chemotherapy alone. The most common grade 3 or higher TRAEs was decreased neutrophil count (Jia et al., 2025). Similarly, other trials have combined anti-angiogenic agents like anlotinib or bevacizumab with PD-1 inhibitors have shown promising response rates and survival benefits (Sha et al., 2024; Ying et al., 2025). These results confirm that vascular normalization can synergize with immunotherapy to enhance the anti-tumor immune response in pancreatic adenocarcinoma.

JDB153 is a unique dual inhibitor that targets both MNK and VEGFR, simultaneously suppressing the translation of oncogenic proteins and inducing tumor vascular normalization. Preclinical models in non-small cell lung cancer have demonstrated that JDB153 exhibits anti-tumor activity and synergizes with anti-PD-1 therapy (Xu et al., 2025). Our team previously conducted a phase II study of serplulimab combined with GnP chemotherapy and radiotherapy. That study confirmed that serplulimab is well tolerated in advanced pancreatic cancer (Cheng et al., 2025). We hypothesize that JDB153 will create a favorable immune environment that allows serplulimab to work effectively.

A major strength of this study is its chemotherapy-free design. Patients in the third-line setting are often frail and cannot tolerate intensive chemotherapy regimens. JDB153 and serplulimab are expected to have a more manageable toxicity profile compared to traditional chemotherapy. Safety is a primary concern and we have implemented a rigorous safety monitoring plan. The study utilizes a Simon’s two-stage design. This allows us to assess preliminary efficacy in a small cohort before expanding enrollment. This protects patients from exposure to an ineffective regimen. The study also includes a comprehensive biomarker analysis. We will analyze tumor tissue and blood samples to investigate changes in the immune microenvironment and translational machinery. Understanding these biological changes will help us identify which patients are most likely to benefit from this combination. It may also reveal mechanisms of resistance that could inform future research.

There are limitations of this study. As a single-arm, phase Ib/II study, the sample size is relatively small. The lack of a randomized control arm limits our ability to definitively compare efficacy against other potential palliative treatments. However, given the lack of standard care in this setting, comparing results against historical controls is a valid approach for early-phase investigation. If the primary endpoints are met, larger randomized clinical trials will be necessary to confirm these findings.

In conclusion, this study explores a novel therapeutic combination for a patient population with significant unmet needs. By integrating MNK inhibition, VEGFR inhibition, and PD-1 blockade, we aim to overcome the immunosuppressive barriers of pancreatic cancer. This research will provide valuable evidence regarding the clinical application of combining translational and angiogenic inhibitors with immunotherapy. Ultimately, we hope to establish a new, effective, and well-tolerated treatment option for patients with advanced pancreatic cancer.

